---

## STUDY SYNOPSIS

|                                        |                                                                                                                                                                                                                                                                                                                                                                                                                                                                                                                                                                                                                                                                                                                                                                                                                                                                                                                                                                                                                                     |
|----------------------------------------|-------------------------------------------------------------------------------------------------------------------------------------------------------------------------------------------------------------------------------------------------------------------------------------------------------------------------------------------------------------------------------------------------------------------------------------------------------------------------------------------------------------------------------------------------------------------------------------------------------------------------------------------------------------------------------------------------------------------------------------------------------------------------------------------------------------------------------------------------------------------------------------------------------------------------------------------------------------------------------------------------------------------------------------|
| Sponsor / Sponsor-Investigator  | [name]. med. [name]                                                                                                                                                                                                                                                                                                                                                                                                                                                                                                                                                                                                                                                                                                                                                                                                                                                                                                                                                                                                    |
| Study Title:                    | Glucocorticoid withdrawal and glucocorticoid-induced adrenal insufficiency: a randomized controlled multicenter trial.                                                                                                                                                                                                                                                                                                                                                                                                                                                                                                                                                                                                                                                                                                                                                                                                                                                                                                              |
| Short Title / Study ID:         | Taper Or Abrupt Steroid STop: the TOASST trial.                                                                                                                                                                                                                                                                                                                                                                                                                                                                                                                                                                                                                                                                                                                                                                                                                                                                                                                                                                                     |
| Protocol Version and Date:      | Version 3.1; Date: 24.08. 2021                                                                                                                                                                                                                                                                                                                                                                                                                                                                                                                                                                                                                                                                                                                                                                                                                                                                                                                                                                                                      |
| Trial registration:             | ClinicalTrials.gov Identifier: NCT03153527
Eudra CT Nr: 2020-005601-48                                                                                                                                                                                                                                                                                                                                                                                                                                                                                                                                                                                                                                                                                                                                                                                                                                                                                                                                                           |
| Study category and Rationale    | B; clinical trial with humans testing a drug registered in Switzerland and the European Union (Prednisone) versus placebo.                                                                                                                                                                                                                                                                                                                                                                                                                                                                                                                                                                                                                                                                                                                                                                                                                                                                                                          |
| Clinical Phase:                 | IV                                                                                                                                                                                                                                                                                                                                                                                                                                                                                                                                                                                                                                                                                                                                                                                                                                                                                                                                                                                                                                  |
| Background and Rationale:       | No data from controlled trials are available on whether and how to taper glucocorticoids. We aim to establish the safety of rapidly terminating prednisone treatment irrespective of biochemical status of the hypothalamic-pituitary-adrenal axis, provided glucocorticoid cover is ensured in situations of stress. Health conditions are inflammatory, autoimmune, and others except s/p organ transplantation or primary adrenal failure.                                                                                                                                                                                                                                                                                                                                                                                                                                                                                                                                                                                       |
| Objective(s):                   | 1°: To test the hypothesis that in patients treated with systemic glucocorticoids for various inflammatory disorders, rapid termination of treatment will not result in a worse clinical outcome than a tapering regime over four weeks.
2°: To test whether the 250 mcg ACTH test predicts the need of unplanned glucocorticoid treatment during 6 months of follow-up. To establish the relationship between clinical signs and symptoms of hypocortisolism and biochemical adrenocortical performance.                                                                                                                                                                                                                                                                                                                                                                                                                                                                                                                        |
| Outcome(s):                     | 1°: Time to first occurrence of hospitalization, death, initiation of unplanned systemic glucocorticoid therapy, or adrenal crisis.

Main 2°: Time to first occurrence of individual components of the primary outcome; Cumulative overall systemic glucocorticoid dose; Cumulative systemic glucocorticoid dose administered to treat or prevent adrenal failure; Cumulative systemic glucocorticoid dose administered to treat relapse of disease, specified for each disease                                                                                                                                                                                                                                                                                                                                                                                                                                                                                                                                               |
| Study design:                   | Randomized controlled noninferiority trial.                                                                                                                                                                                                                                                                                                                                                                                                                                                                                                                                                                                                                                                                                                                                                                                                                                                                                                                                                                                         |
| Inclusion / Exclusion criteria: | 
Patients with a variety of inflammatory disorders will be eligible, e.g. sarcoidosis, inflammatory bowel disease, polymyalgia rheumatica, rheumatoid arthritis, giant cell arthritis, autoimmune hemolytic anemia, and other autoimmune disease.
 
Inclusion criteria: Age <math>\geq</math> 18 years; daily glucocorticoid dose <math>\geq</math> 7.5 mg prednisone-equivalent at the time of inclusion; therapy over <math>\geq</math> 28 days with a cumulative glucocorticoid dose <math>\geq</math> 420 mg prednisone-equivalent prior to inclusion; tapering not or no longer mandatory to treat underlying disease.
 
Exclusion criteria: Primary adrenal failure; pregnancy; treatment with systemic depot glucocorticoids (e.g. intramuscular, epidural); incapability to administer glucocorticoid cover treatment in situations of stress; inability or unwillingness to provide informed consent; untreated hereditary galactose intolerance or lactase deficiency or glucose-galactose malabsorption.
 |

|                                               |                                                                                                                                                                                                                                                                                                                                                                                                                                                                                                                                                                                                                                                                                                                                                                                                                                                                                                                                                                                                                                     |
|-----------------------------------------------|-------------------------------------------------------------------------------------------------------------------------------------------------------------------------------------------------------------------------------------------------------------------------------------------------------------------------------------------------------------------------------------------------------------------------------------------------------------------------------------------------------------------------------------------------------------------------------------------------------------------------------------------------------------------------------------------------------------------------------------------------------------------------------------------------------------------------------------------------------------------------------------------------------------------------------------------------------------------------------------------------------------------------------------|
| Measurements and procedures:           | Patients on glucocorticoid treatment (cumulative dose $\geq 420$ mg prednisone-equivalent over $\geq 28$ days; current daily dose $\geq 7.5$ mg prednisone-equivalent) are eligible if the treating physician deems it feasible to end the glucocorticoid therapy. Participants will be randomized 1:1 (day 0) to abrupt treatment stop (intervention arm) or tapering over 4 weeks (standard treatment arm). A 250 mcg ACTH test will be performed upon randomization, the result of which will be blinded to treating physicians and investigators. Patients will be followed-up by telephone interview (days 7, 35, 90 180). In a subgroup of 180 patients, clinical visits will be performed on days 7 and 35, including an interview, measurement of vital parameters, and a 250 mcg ACTH test.                                                                                                                                                                                                                                |
| Study Product / Intervention:          | Placebo group (intervention arm):
Stop glucocorticoid treatment; administer placebo matching the verum preparation in weekly intervals (cf. next section).                                                                                                                                                                                                                                                                                                                                                                                                                                                                                                                                                                                                                                                                                                                                                                                                                                                                       |
| Control Intervention (if applicable):  | Verum group (control/standard arm):
If patient is on $> 7.5$ mg prednisone-equivalent daily: administer 7.5 mg q.d. for 7 days, then 5 mg q.d. for 7 days, then 2.5 mg q.d. for 7 days, then 2.5 mg q.d. every other day for 7 days, then stop. If patient on 7.5 mg q.d.: maintain for 7 days, then taper as above.                                                                                                                                                                                                                                                                                                                                                                                                                                                                                                                                                                                                                                                                                                             |
| Number of Participants with Rationale: | Total number of participants in both arms: 573 (95% CI: 565 to 580).                                                                                                                                                                                                                                                                                                                                                                                                                                                                                                                                                                                                                                                                                                                                                                                                                                                                                                                                                                |
| Study Duration:                        | 7.5 years                                                                                                                                                                                                                                                                                                                                                                                                                                                                                                                                                                                                                                                                                                                                                                                                                                                                                                                                                                                                                           |
| Study Schedule:                        | First-Participant-In: June 2017
Last-Participant-Out (planned): December 2024                                                                                                                                                                                                                                                                                                                                                                                                                                                                                                                                                                                                                                                                                                                                                                                                                                                                                                                                                    |

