
From our own observations on adrenal function in participants of the “REDUCE” trial and previously published literature, we have generated the hypothesis that in patients treated with systemic glucocorticoids for a variety of disorders, it is feasible and safe to rapidly terminate steroid therapy irrespective of biochemical status of the HPA axis, provided glucocorticoid cover is ensured in situations of stress. The primary purpose of the study is to establish feasibility and safety of rapidly terminating systemic glucocorticoid treatment, irrespective of biochemical status of the HPA axis. The secondary purpose of the study is to assess the usefulness of the 250 mcg ACTH test to predict the clinical outcome with respect to the primary outcome.

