In the intervention (placebo) arm, there is the potential benefit of reducing the cumulative prednisone dose, thereby minimizing the exposure to as well as untoward effects of glucocorticoids. Other benefits include the generation of evidence regarding the potential of the 250 mcg ACTH test to stratify patients regarding the need for tapering and the prediction of future glucocorticoid demand; as well as regarding the correlation of biochemical and clinical parameters of adrenal insufficiency.

We know of no competing trial to our study.

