### **4.3 Secondary Objectives**

The secondary objectives of this trial are:

- To establish the clinical relevance of the 250 mcg ACTH (Synacthen®) stimulation test.
- To establish the relationship between clinical signs and symptoms of hypocortisolism and biochemical adrenocortical performance

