## 5. STUDY OUTCOMES

### 5.1 Primary Outcome

The composite primary outcome is:

Time to first occurrence of hospitalization, death, initiation of unplanned systemic glucocorticoid therapy, or adrenal crisis (defined as glucocorticoid-responsive hypotension or shock with or without accompanying symptoms and signs such as weakness, apathy, nausea, vomiting, abdominal pain, hypothermia, hyponatremia [serum sodium < 135 mM], hyperkalemia [serum potassium > 5 mM], hypoglycemia [plasma glucose < 3.5 mM]); whichever occurs first.

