#### 11.4.3 Secondary Analyses

Secondary outcomes:

**Performance of the 250 mcg corticotropin stimulation test.** If this test is clinically relevant, it is assumed that in patients with a normal test result, the two study arms will not differ with regard to the primary outcome, whereas patients with a pathological test result will experience an event more often after the rapid termination (experimental arm) than after tapering (control arm). It is thus hypothesized that there is an interaction between the test result and the glucocorticoid withdrawal scheme. To test for a significant interaction, the Cox proportional hazard regression model used to assess the primary objective is extended by the stimulation test result (passed vs. failed) and its interaction with the treatment group (rapid vs. tapering). If a significant interaction is found, subgroup analyses are performed for the two treatment groups in order to estimate the strength of the association between test result and primary outcome.

---

**The time to first occurrence of individual components** of the primary outcome is, in analogy to the (composite) primary outcome, also analysed with Cox proportional hazards regression models.

Cumulative overall systemic glucocorticoid dose, cumulative systemic glucocorticoid dose administered to treat or prevent adrenal failure, cumulative systemic glucocorticoid dose administered to treat relapse of disease (specified for each disease), general health status as self-assessed by the patients on a VAS, blood pressure (supine and standing), hospital length of stay, weakness, hypothermia, nausea, vomiting, abdominal pain, and fatigue are analysed with linear regression models.

In all analyses, the variables for which randomisation was stratified (center and age group) are included as covariates for adjustment. If model assumptions are not met, transformations of outcome variables and the use of generalised linear (instead of linear) models are considered.

Besides the secondary outcomes, potential glucocorticoid-induced side effects will be assessed and documented on the CRF. Proportions of side effects will be compared between treatment groups and analyzed using logistic regression.

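### The ACTH-test objective is stated on two different outcomes, and the one named in the synopsis, need for unplanned glucocorticoid treatment, has no analysis in the protocol

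*Protocol*

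**What the plan says.** The protocol describes the purpose of the ACTH test in several places, and they do not agree on the outcome.

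- **Synopsis, Objective(s):** "To test whether the 250 mcg ACTH test predicts the need of unplanned glucocorticoid treatment during 6 months of follow-up". The outcome is glucocorticoid need.
- **Section 3.7, potential benefits:** the test may inform "the need for tapering and the prediction of future glucocorticoid demand". This also points to glucocorticoid need.
- **Section 3.1:** the secondary purpose is "to assess the usefulness of the 250 mcg ACTH test to predict the clinical outcome with respect to the primary outcome". The outcome is the composite.
- **German lay summary:** it lists the composite events and then says the study will examine whether the test can predict them.
- **Section 4.3:** "To establish the clinical relevance of the 250 mcg ACTH (Synacthen®) stimulation test". No outcome is named.

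Section 5.1 defines the composite as "Time to first occurrence of hospitalization, death, initiation of unplanned systemic glucocorticoid therapy, or adrenal crisis".

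Section 11.4.3 fixes one ACTH-test analysis: "the Cox proportional hazard regression model used to assess the primary objective is extended by the stimulation test result (passed vs. failed"), together with its interaction with treatment group. It continues: "If a significant interaction is found, subgroup analyses are performed for the two treatment groups in order to estimate the strength of the association", and that association is with the primary outcome. The individual components get their own Cox models by analogy with the primary analysis, with no test-result term mentioned. The subgroup list in the same section includes the test result but names no outcome.

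**The concern.** The two versions of the objective count different patients as events. A patient admitted for an unrelated reason, with no glucocorticoid started, is an event in the section 11.4.3 model but not under the synopsis objective. No described analysis puts the test result into a model of unplanned glucocorticoid therapy.

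Two things are at stake. First, the ACTH test measures adrenal reserve. If admissions and deaths have little to do with adrenal reserve, they pull the composite hazard ratio towards 1, and a null composite result could be reported as showing that the test is not clinically relevant although the outcome in the synopsis was never modelled. Second, with two outcomes on paper, the choice between them would be made after the results are known unless it is settled beforehand.

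**Working it through.** **The protocol's own figures.** The critical hazard ratio is ln(0.47)/ln(0.60) = 1.478, as stated. It needs 206 events (Schoenfeld, two-sided 5%, 80% power); 206/0.40 = 515, and 515/0.90 rounds up to 573, as stated. These belong to the primary analysis and neither support nor weaken this point.

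**Coverage of each version of the objective.**

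| Version of the objective | Where stated | Analysis in 11.4.3 |
|---|---|---|
| Test predicts primary composite | 3.1, lay summary | Composite Cox model with test result and test-by-arm interaction |
| Test predicts unplanned glucocorticoid need | Synopsis, echoed in 3.7 | None described |

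**Size of a possible dilution.** The protocol gives neither component rates nor an expected effect of the test result, so this is a range under assumptions.

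Inputs:
- Composite risk 40% at 6 months (11.2).
- One third of patients fail the test. This is an assumption; section 5.4 reports about that share with suppressed adrenals at discharge in the earlier trial.
- Glucocorticoid-start risk r of 25%, 30% or 35% averaged over all patients (assumed).
- True hazard ratio h = 1.5 for failed versus passed on glucocorticoid starts, and no relation of the other components to the test (assumed).

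Formulas, with hazards over 6 months:
- Other-component hazard: o = −ln(0.60) + ln(1 − r).
- Glucocorticoid hazard in patients who pass: b = −ln(1 − r) / (2/3 + h/3). For h = 1.5 the divisor is 1.1667.
- Composite hazard ratio: (b·h + o)/(b + o).

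Results:
- r = 25%: b = 0.2466, o = 0.2231; (0.3699 + 0.2231)/0.4697 = 1.26.
- r = 30%: b = 0.3057, o = 0.1542; (0.4586 + 0.1542)/0.4599 = 1.33.
- r = 35%: b = 0.3692, o = 0.0800; (0.5538 + 0.0800)/0.4492 = 1.41.

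Approximate power for a main effect of the test result is Φ(ln HR × √(d × 1/3 × 2/3) − 1.96), with d = 573 × 0.95 × risk. The factor 0.95 reflects 10% drop-out spread evenly over follow-up. The composite has d of about 218.

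| r | Glucocorticoid events | Power, glucocorticoid outcome | Power, composite |
|---|---|---|---|
| 25% | 136 | 61% | 37% |
| 30% | 163 | 69% | 51% |
| 35% | 191 | 75% | 67% |

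These are not the power of the planned test, which is a test-by-arm interaction. They only show how the choice of outcome changes an association.

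**The case against.** A reader might infer that the ACTH objective is not tested at all. The documents do not support that. Section 3.1 and the lay summary set it on the primary-outcome events, and section 11.4.3 matches them. Nothing shows that the synopsis is the authoritative version. This part of the objection stands: the defect is an inconsistency that leaves one version without an analysis.

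A reader might also infer that admissions and deaths are known to dilute the association. The protocol gives no component rates. Section 11.2 says the 40% rests on expected relapse rates, with other components adding to it, which suggests that glucocorticoid-treated flares may dominate; the loss would then be modest, as at r = 35%. The other components may also be related to the test. Adrenal crisis is glucocorticoid-responsive by definition, and section 3.6 provides glucocorticoid cover for acute illness and operations, so admissions and glucocorticoid starts may coincide. Dilution is therefore conditional.

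A further tempting step is to call for a model of time to glucocorticoid started for adrenal failure. Secondary outcome 3 is a cumulative dose to treat or prevent adrenal failure, and the protocol does not show that a start date by indication is recorded.

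Finally, section 11.4 leaves detailed methodology to a statistical analysis plan that is not at hand and may add such a model. That does not remove the contradiction. The protocol itself fixes the composite for this analysis, and section 11.4 treats departures from its described analyses as deviations to be listed.

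**Conclusion.** The point holds as an inconsistency between objective and analysis. The synopsis objective, echoed in section 3.7, has no analysis in the protocol; the version in section 3.1 does. This follows from the text and needs no assumption.

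The possible cost is conditional. With one third failing the test, a 40% composite risk and other components unrelated to the test, a true hazard ratio of 1.5 on glucocorticoid starts would appear as about 1.26 to 1.41 on the composite for glucocorticoid risks of 25% to 35%. It would be smaller still if glucocorticoid starts make up nearly all events or if the other components also track the test result.

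Only a secondary objective is affected. The primary non-inferiority conclusion does not change.

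**What to change.** - In section 11.4.3, add a model of time to unplanned systemic glucocorticoid therapy, already part of secondary outcome 1, with test result, arm and the randomisation strata. Treat death as a competing event, since it prevents a later glucocorticoid start.
- Report the test-result association from this model whatever the composite model shows. As written, the association is estimated only after a significant interaction, and a test that predicts equally well in both arms would meet that condition only about 5% of the time.
- Keep the composite analysis alongside it.
- Make the synopsis, 3.1 and 4.3 name the same outcome or outcomes.
- Do not add a time-to-start model for adrenal failure unless start date by indication is recorded. Otherwise, relate the test result to the cumulative dose in secondary outcome 3, noting that it includes preventive use.

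The cost is one or two more secondary models and wording changes in a few sections. The first model uses an outcome already planned and needs no new visit or larger sample.
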